## 15.9 ANALYSIS OF PRIMARY ENDPOINT

The primary endpoint is defined as the AUC of WURSS-21 QoL composite subscore assessed during first 8 days of symptoms.

The WURSS-21 QoL composite subscore is calculated by summing the scores of the 9 consecutive items of WURSS-21, from item 12 (“think clearly”) to item 20 (“live your personal life”), as documented in the subject diary (see 13.6.1). The AUC will be assessed by applying the trapezoidal approximation.

The confirmatory analysis of the primary endpoint will be performed for the full analysis set. Exploratory analyses will be performed for the per-protocol analysis set.

Data of the primary endpoint will be summarized by descriptive statistics using appropriate tabulation.

The two-sided confirmatory null-hypothesis will be tested with the non-parametric two-sided Wilcoxon (Mann-Whitney) rank-sum test.

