## 11.6 METHODS OF RANDOMISATION AND BLINDING

The clinical investigation will be conducted in a double-blind randomised manner (block randomisation). The subjects will be randomised at the screening visit. The randomisation list will be provided to the sponsor's assigned responsible person (not involved in the study) by the statistician responsible for generation of the randomisation list. The ratio of randomisation between the verum and placebo will be 1:1. Random numbers will be assigned to the subjects in a sequential order based on time of randomisation at each investigational site (several whole blocks will be allocated to each centre). Randomisation list will be concealed to the investigational sites. It will be stored under lock and key by the sponsor until database closure. After database closure and sign-off of the statistical analysis plan, the sponsor's responsible person will provide the randomisation list to the statistician responsible for the statistical analysis (and the project manager at the CRO, as appropriate).

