### 15.1 STATISTICAL HYPOTHESES

A lower value of the primary endpoint (i.e., AUC of WURSS-21 QoL composite subscore assessed during first 8 days of symptoms) corresponds to fewer complaints, a higher value corresponds to more complaints. The study is aiming to show superiority of CMS008618 compared to placebo, i.e. aiming at lower values of the AUC values in the verum group compared to the placebo group.

The null hypothesis  $H_0$  and the alternative hypothesis  $H_A$  for the confirmatory analysis of the primary endpoint are formulated as follows:

- $H_0$ :  $\mu_{\text{verum}} = \mu_{\text{placebo}}$ , i.e. no difference between verum and placebo with respect to the primary endpoint.
- $H_A$ :  $\mu_{\text{verum}} \neq \mu_{\text{placebo}}$ , i.e. difference between verum and placebo with respect to the primary endpoint.

The null hypotheses  $H_0$  and the alternative hypotheses  $H_A$  for the major secondary endpoints are formulated analogously.

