### 15.2 SIGNIFICANCE LEVEL

The confirmatory type I error rate for the study is set to 0.05 (two-sided). Due to the testing of a-priori ordered hypotheses, no multiplicity correction is considered necessary (Points to consider on multiplicity issues in clinical trials, CPMP/EWP/908/99, 2002).

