### 15.3 SAMPLE SIZE CALCULATION

The sample size for the present study is calculated so that the comparison of the verum treatment group and the placebo treatment group for the primary endpoint has 90% power to detect a relevant clinical effect size  $\delta$  (i.e., the ratio of the absolute val-

ue of the difference between two means and the standard deviation) with a two-sided significance level  $\alpha=0.05$  as outlined below.

Based on the results of a previously conducted trial with the same IP in a comparable setting (sponsor's data on file), the difference between the verum group and the placebo group regarding the mean AUC of the WURSS-21 QoL composite subscore during first 8 days of symptoms is expected to be at least 33.900. The associated common standard deviation  $\sigma$  is expected to be 92.700. Therefore, the relevant clinical effect size  $\delta = |\mu_{\text{verum}} - \mu_{\text{placebo}}| / \sigma$  (i.e. the ratio of the difference between verum and placebo and the standard deviation) which should be detected with adequate power is assumed to be 0.366. This corresponds to  $p_1 = P(X < Y) = 0.602$  which is the probability that an observation, X, in group 1 will be less than an observation Y in group 2 when the alternative hypothesis is true. The null hypothesis being tested is that  $p_1 = 0.5$ .

Under these assumptions, a sample size of  $n = 169$  subjects in each treatment group will have 90% power to detect a probability of 0.602 that an observation in the verum group is less than an observation in the placebo group using a Wilcoxon (Mann-Whitney) rank-sum test with a 0.05 two-sided significance level (nQuery Advisor® Release 7.0).

Based on the sample size in the study and taking into account an assumption for a power of 80%, an effect size of 0.315 with regard to the main secondary endpoints (Jackson score AUC and exposure to relevant concomitant medication) would be detectable (with a power of 80% and a sample size of  $n = 169$  subjects in each treatment group,  $p_1 = P(X < Y) = 0.588$  is calculated, corresponding to an effect size  $d = 0.315$ .)

Thus, considering the planned 1:1 randomization with two treatment groups,  $n = 338$  subjects (with  $n = 169$  subjects per treatment group) are required for the primary confirmatory statistical analysis of the study.

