## 15.10 ANALYSIS OF MAJOR SECONDARY ENDPOINTS

The major secondary endpoints are ranked according to clinical relevance as:

1. AUC days 1-8 composite daily severity of all symptoms within the Jackson score (mean of morning and evening) (day 1 is the first day of symptom recording). The two-sided confirmatory null-hypothesis will be tested with the non-parametric two-sided Wilcoxon (Mann-Whitney) rank-sum test.
2. Exposure to any concomitant treatment (including natural health products) that may affect common cold symptoms - immune suppressants/immune stimulants, analgesics/anti-rheumatics, anti-phlogistics, antitussives/expectorants, mouth or throat therapeutics, decongestants, antibiotics, anti-histaminergic drugs, nasal drops/spray or any medication/treatment known to affect common cold symptoms - at any dose, expressed as number of days with concomitant treatment during the first 4 days for each subject (based on diary data). The two-sided confirmatory null-hypothesis for the second major secondary endpoint will be tested using the non-parametric two-sided Wilcoxon (Mann-Whitney) rank-sum test.

In order to control the overall type I error rate, the primary endpoint and the two major secondary endpoints will be tested in a fixed sequence as a-priori ordered hypotheses. That is, the first major secondary endpoint will be tested only if the primary endpoint is positive (ie,  $p < 0.05$ ), and the second major secondary endpoint will be tested

only if the first major secondary endpoint is positive. No confirmatory claims will be based on endpoints that have a rank lower than or equal to that variable whose null hypothesis is the first that could not be rejected.

The confirmatory analysis of the major secondary endpoints will be performed for the full analysis set. Exploratory analyses will be performed for the per-protocol analysis set.

Data of the major secondary endpoints will be summarized by descriptive statistics using appropriate tabulation.

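### The confirmatory rank-sum tests leave unused a severity score recorded before the first dose and, if several sites take part, the centre within which blocks are allocated

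*Protocol*

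**What the plan says.** **Test.** Section 15.9 has the primary endpoint "tested with the non-parametric two-sided Wilcoxon (Mann-Whitney) rank-sum test". Section 15.10 names the same test for the Jackson AUC and for days with concomitant treatment. None of the three has a stratum or a covariate.

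**Randomisation.** Section 11.6 plans 1:1 block randomisation in which "several whole blocks will be allocated to each centre", so centre is in effect a stratum. The number of centres is not given. The synopsis has a single entry for the investigation site, while 11.6 speaks of each site.

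**Pre-dose score.** Sections 11.3 and 11.9.2 let use of the product start only after a yes answer in the daily diary and a Jackson score of at least 1 for a symptom other than headache.

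**Planned adjustment.** Section 15.14 plans a nonparametric covariance analysis with the baseline WURSS-21 QoL subscore, labelled exploratory. Baseline is not defined there. Section 13.6.1 collects that scale once daily, in the evening, from the day the cold diary starts.

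**Null and gate.** Section 15.1 writes the null as equal mu in the two arms and explains it as "no difference between verum and placebo with respect to the primary endpoint". Section 15.3 says "The null hypothesis being tested is that" p1 = 0.5. In 15.10, "the first major secondary endpoint will be tested only if the primary endpoint is positive", where positive means p < 0.05 and no direction is named.

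**The concern.** How ill a subject is when the product is first used may well predict the symptom burden over the next 8 days. A score taken at that moment, before any dose, is a natural covariate: treatment cannot have affected it, and it costs nothing to use. A confirmatory test that leaves it out carries avoidable noise. The same holds, more weakly, for centre when allocation is balanced within centre and the test ignores that balance.

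The one adjusted analysis in the plan does not fill the gap. It is exploratory, and its covariate can be an evening value recorded after several doses. Adjusting for a value that treatment may already have changed can remove part of the effect.

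Two points of wording belong with this. Sections 15.1 and 15.3 name different nulls for the same test. And the gate in 15.10, read literally, would also open on a significant result in favour of placebo.

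**Working it through.** **1. The plan's own figure.** Inputs from 15.3: the difference in the mean AUC "composite subscore during first 8 days of symptoms is expected to be at least 33.900", the common SD is 92.7, alpha is 0.05 two-sided, and 169 "subjects in each treatment group will have 90% power to detect a probability of 0.602".

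- d = 33.9/92.7 = 0.3657
- p1 = Φ(d/√2) = 0.602
- n per group = (1.960 + 1.282)² / [6 × (0.602 − 0.5)²] = 168.3, rounded up to 169, as stated
- Power at 169 = Φ(0.102 × √(6 × 169) − 1.960) = 90.1%
- Power at 200 per arm (the 400 treated subjects of 15.3) = 94.2%

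The sample size is right for the unadjusted test.

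**2. Adjusting for the pre-dose Jackson total.** The correlation r between this score and the AUC is not in the protocol. I assume 0.3 to 0.5. Adjustment scales the residual SD by √(1 − r²), so the effect becomes d/√(1 − r²). The number needed is about 168.3 × (1 − r²).

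| r (assumed) | d adjusted | p1 | Power at 169 per arm | n per arm for 90% |
|---|---|---|---|---|
| 0 | 0.366 | 0.602 | 90.1% | 169 |
| 0.3 | 0.383 | 0.607 | 92.5% | 154 |
| 0.4 | 0.399 | 0.611 | 94.3% | 142 |
| 0.5 | 0.422 | 0.617 | 96.2% | 127 |

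Simulating a rank analysis of covariance on normal data at 169 per arm agrees: about 93% power at r = 0.3, about 96% at r = 0.5, no material loss at r = 0, and type I error near 5%.

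**3. Stratifying by centre.** Assumptions: 320 subjects, blocks of four within centre, d = 0.366, 4,000 runs per setting. Each cell gives the result for 5 / 10 centres.

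| ICC (assumed) | Type I, plain | Type I, stratified | Power, plain | Power, stratified |
|---|---|---|---|---|
| 0 | 5.3 / 5.2% | 5.2 / 5.4% | 88.9 / 89.3% | 88.3 / 88.2% |
| 0.05 | 4.4 / 4.6% | 4.6 / 5.1% | 89.4 / 89.3% | 89.8 / 89.5% |
| 0.10 | 4.1 / 4.0% | 5.0 / 4.9% | 90.9 / 90.6% | 92.1 / 91.5% |
| 0.20 | 3.2 / 3.1% | 4.9 / 4.7% | 91.5 / 92.5% | 94.1 / 94.5% |

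Ignoring centre makes the plain test conservative. The gain from stratifying is about 1 point or less up to an ICC of 0.10. With no centre effect, stratifying costs up to about 1 point.

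**4. The two nulls.** Section 15.3 converts the mean difference to p1 through Φ(d/√2) with one common SD. For normal data differing only in location, equal means and p1 = 0.5 are the same statement. Outside that model they can part, and the rank-sum test then addresses p1, or equality of distribution.

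**The case against.** The plain rank-sum test is valid, prespecified and matched to the sample size calculation, and leaving out a covariate does not bias a randomised comparison. With 400 treated subjects, power for the assumed effect is 94.2% anyway. Covariate adjustment is already planned in 15.14, and the correlations above are assumptions. All of this stands, and it limits the point to efficiency. It does not remove it, because the analysis in 15.14 is exploratory and its baseline can be post-dose.

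Three stronger readings are tempting, and the protocol supports none of them.

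- *Ignoring the blocking by centre inflates the error rate.* It does the opposite, as the table shows. If the single site entry in the synopsis is right, the matter falls away.
- *The test rejects far too often because 15.1 puts the null on means.* Log-normal AUCs with equal means of 150 but SDs of 80 and 119 are indeed declared different in about half of simulated trials. That example needs unequal SDs, whereas 15.3 assumes a common one, and the arms then truly differ in distribution. When both arms share a distribution, the simulated rejection rate is about 5% (5.2% and 4.5%). Section 15.1 also explains its null simply as no difference, so the mismatch is one of wording.
- *A result favouring placebo could lead to a claim.* Section 15.1 states the aim as lower AUC values under verum, which largely answers this. Only the literal gate in 15.10 lacks the direction.

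**Conclusion.** The point holds as one of efficiency and wording, not validity. The confirmatory tests omit a pre-dose severity score that the starting rule already requires. Using it would raise power at 169 per arm from 90.1% to about 92.5-96%, if its correlation with the AUC is 0.3 to 0.5, and costs essentially nothing if the correlation is zero. Centre is secondary: about 1 point or less for an ICC up to 0.10, and only if more than one site takes part. Both ranges rest on assumed values. The sample size of 169 per group is reproduced, and power is not in doubt under the plan's own assumptions. The different nulls in 15.1 and 15.3 and the directionless gate in 15.10 are minor but worth correcting in the same edit.

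**What to change.** - **15.9 and 15.10:** name one confirmatory test for each endpoint, a rank analysis of covariance adjusted for the Jackson total recorded before the first dose. If several sites take part, stratify it by centre, with small centres pooled by a rule fixed before unblinding. Keep the plain rank-sum test as a sensitivity analysis.
- **Covariate:** define it as the total at the diary entry that met the starting rule in 11.3, and state what is done for a subject who has no such entry. A definition by clock time may not work, because 13.6.1 records use of the product only once daily. For the Jackson AUC the covariate can also enter the day 1 value; adjustment stays valid because the score precedes treatment.
- **15.14:** say which WURSS-21 QoL value is the baseline and that it may be post-dose, or use the pre-dose Jackson total there too.
- **15.1:** restate the null as p1 = 0.5 (no difference in distribution), as in 15.3.
- **15.10:** define positive as two-sided p < 0.05 with the estimate favouring verum.

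The cost is wording in the protocol and SAP before unblinding. No new data and no larger sample are needed.

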## 15.10 ANALYSIS OF MAJOR SECONDARY ENDPOINTS

The major secondary endpoints are ranked according to clinical relevance as:

1. AUC days 1-8 composite daily severity of all symptoms within the Jackson score (mean of morning and evening) (day 1 is the first day of symptom recording). The two-sided confirmatory null-hypothesis will be tested with the non-parametric two-sided Wilcoxon (Mann-Whitney) rank-sum test.
2. Exposure to any concomitant treatment (including natural health products) that may affect common cold symptoms - immune suppressants/immune stimulants, analgesics/anti-rheumatics, anti-phlogistics, antitussives/expectorants, mouth or throat therapeutics, decongestants, antibiotics, anti-histaminergic drugs, nasal drops/spray or any medication/treatment known to affect common cold symptoms - at any dose, expressed as number of days with concomitant treatment during the first 4 days for each subject (based on diary data). The two-sided confirmatory null-hypothesis for the second major secondary endpoint will be tested using the non-parametric two-sided Wilcoxon (Mann-Whitney) rank-sum test.

In order to control the overall type I error rate, the primary endpoint and the two major secondary endpoints will be tested in a fixed sequence as a-priori ordered hypotheses. That is, the first major secondary endpoint will be tested only if the primary endpoint is positive (ie,  $p < 0.05$ ), and the second major secondary endpoint will be tested

only if the first major secondary endpoint is positive. No confirmatory claims will be based on endpoints that have a rank lower than or equal to that variable whose null hypothesis is the first that could not be rejected.

The confirmatory analysis of the major secondary endpoints will be performed for the full analysis set. Exploratory analyses will be performed for the per-protocol analysis set.

Data of the major secondary endpoints will be summarized by descriptive statistics using appropriate tabulation.

#### 15.11 ANALYSIS OF OTHER SECONDARY ENDPOINTS

Analyses of other secondary endpoints will be performed primarily for the full analysis set and for selected parameters also for the per-protocol analysis set. All other secondary endpoints will be analyzed exploratory only and will be descriptively assessed. For continuous data, standard statistical characteristics will be presented (number of subjects with non-missing data, mean, standard deviation, median, minimum and maximum and quartiles). The values of continuous data may also be transformed into categorical ordinal classes according to clinical criteria to determine their frequency distribution. Categorical data (nominal or ordinal) will be summarized using frequency tables.

Continuous other secondary endpoints will be analyzed for between-group comparison using the non-parametric two-sided Mann-Whitney-U-test. Multiple testing will be performed without exploratory adjustment for multiple testing. For categorical other secondary endpoints chi tests will be used for between-group comparison.

A more detailed description of the planned descriptive and exploratory analyses will be presented in the SAP.

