### 8.3 OTHER SECONDARY ENDPOINTS

To be assessed in comparison between verum and placebo:

- AUC days 1-8 for each single WURSS-21 QoL subscore item
- AUC days 1-8 composite daily severity of all local symptoms within the Jackson score (mean of morning and evening)
- AUC days 1-8 composite daily severity of each individual symptom of the Jackson score (mean of morning and evening)
- Frequency of subjects with use of concomitant treatment (including natural health products) that may affect common cold symptoms - immune suppressants/immune stimulants, analgesics/anti-rheumatics, anti-phlogistics, antitussives/expectorants, mouth or throat therapeutics, decongestants, antibiotics, anti-histaminergic drugs, nasal drops/spray or any medication/treatment known to affect common cold symptoms - at any dose, during days 1-4 (based on diary data)

- Assessment of duration of first intense phase, expressed as number of days from start of treatment until scoring <5 in total Jackson score
- Assessment of symptom intensity, expressed as mean total Jackson score days 1-4
- Assessment of symptom sore throat per Sore Throat Scale, expressed as AUC days 1-8
- Percentage of subjects with confirmed common cold at Visit 2 (from all subjects with V2)
- Global evaluation of efficacy by subjects and investigators at study end

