#### **13.2.2 Visit 3 (V3, Final), 16 ± 4 Days After Symptom Start**

- Questioning and documentation of possible occurrence of AEs/device deficiencies

cies

- Questioning and documentation of new or changed concomitant treatment
- Return and control of the subject diary
- Return of IP and accountability
- Physical examination
- Measurement of blood pressure and pulse rate
- Global evaluation of efficacy by subjects and investigators (4-point categorical scale)
- Global evaluation of tolerability by subjects and investigators (4-point categorical scale)

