### **13.6.3 Global Evaluation of Efficacy by the Subjects and Investigators**

The subjects and the investigators will evaluate independently the efficacy of the IP by means of a global scaled evaluation with "very good", "good", "moderate" and "poor" at study end.

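### The ordered 4-point global efficacy ratings are assigned a chi-square test that, on its plain reading, ignores the ordering; a rank test already in the plan would have more power against a consistent shift

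*Protocol*

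**What the plan says.** Protocol section 8.3 lists "Global evaluation of efficacy by subjects and investigators at study end" among the other secondary endpoints, all to be compared between verum and placebo. Section 13.2.2 calls the scale a 4-point categorical one. Section 13.6.3 has subjects and investigators rate independently, using a "global scaled evaluation with 'very good', 'good', 'moderate' and 'poor' at study end".

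Section 15.11 sets the analysis:

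- Status: "All other secondary endpoints will be analyzed exploratory only and will be descriptively assessed".
- Description: "Categorical data (nominal or ordinal) will be summarized using frequency tables".
- Test for continuous endpoints: "Continuous other secondary endpoints will be analyzed for between-group comparison using the non-parametric two-sided Mann-Whitney-U-test".
- Test for categorical endpoints: "For categorical other secondary endpoints chi 2 tests will be used for between-group comparison".

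The Biometry entry of the synopsis gives the same rule. Neither place names a trend test or any other test for ordered categories. Both leave further detail to the SAP.

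**The concern.** The four levels run from best to worst, and the study asks whether verum is better than placebo. An ordinary chi-square test on a 2 × 4 table gives the same p-value however the columns are arranged. It spreads its power over three degrees of freedom, that is, over every way the two distributions can differ, including patterns in which neither arm is better overall. A test that uses the ordering concentrates on one degree of freedom: a shift up or down the scale.

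The plan handles similar data differently elsewhere. The second major secondary endpoint (section 15.10) is the number of days with concomitant treatment in the first 4 days. It can take only five values, 0 to 4, so it will be heavily tied, and it is tested with the Wilcoxon rank-sum test. A 4-level ordered rating is the same kind of variable.

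At stake is the chance that a real, consistent improvement in either global rating shows up in its between-group test.

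**Working it through.** **1. The plan's own figure.** The protocol states no power for the global ratings. Its sample size (section 15.3) is for the primary endpoint, and it reproduces:

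- Effect size: 33.9 / 92.7 = 0.366.
- p₁ = Φ(0.366 / √2) = 0.602.
- n per group = (1.960 + 1.282)² / [6 × (0.602 − 0.5)²] = 10.51 / 0.0624 = 168.3, rounded up to 169.

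Section 15.3 then plans 400 treated subjects, about 200 per arm under 1:1 allocation (section 11.6). I use 200 per arm, with 169 as a check, and a two-sided 5% level.

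**2. Assumed inputs.** The protocol gives neither a rating distribution nor an expected effect. I assumed placebo distributions (very good to poor) of 20/40/25/15% and 25/25/25/25%, and proportional-odds shifts of 1.4, 1.6 and 2.0 towards better ratings.

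**3. One case by hand: 20/40/25/15%, odds ratio 1.6, 200 per arm.** Multiply the placebo cumulative odds by 1.6:

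- 0.20/0.80 = 0.25 → 0.40, cumulative 28.6%
- 0.60/0.40 = 1.50 → 2.40, cumulative 70.6%
- 0.85/0.15 = 5.67 → 9.07, cumulative 90.1%

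The verum distribution is therefore 28.6/42.0/19.5/9.9%.

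Noncentrality λ = n Σ (p_V − p_P)² / (p_V + p_P) = 200 × (0.0151 + 0.0005 + 0.0069 + 0.0103) ≈ 6.55.

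- Chi-square, 3 df, critical value 7.81: power 56%.
- Ordered test, 1 df, critical value 3.84, if it captures the whole shift: power 73%.

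**4. Simulation of the 2 × 4 table** (200,000 replicates per cell; Monte Carlo standard error at most √(0.25/200,000) = 0.1 percentage points). Pearson chi-square (3 df) against tie-corrected Mann-Whitney:

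| Placebo ratings | Odds ratio | 200 per arm: chi-square | 200 per arm: Mann-Whitney | 169 per arm: chi-square | 169 per arm: Mann-Whitney |
|---|---|---|---|---|---|
| 20/40/25/15% | 1.4 | 30.6% | 45.3% | 26.4% | 39.7% |
| 20/40/25/15% | 1.6 | 56.0% | 72.8% | 48.2% | 65.6% |
| 20/40/25/15% | 2.0 | 90.2% | 96.6% | 84.1% | 93.5% |
| 25% each | 1.4 | 31.7% | 46.5% | 27.0% | 40.5% |
| 25% each | 1.6 | 57.7% | 74.2% | 50.0% | 66.9% |
| 25% each | 2.0 | 91.1% | 97.0% | 85.4% | 94.2% |

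At an odds ratio of 1.0, both tests reject in 4.9% to 5.1% of replicates. A chi-square test for trend with equally spaced scores stays within one percentage point of Mann-Whitney throughout.

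**5. Cost in sample size, without a rating distribution.** For a shift that a 1-df test captures fully:

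- 80% power needs λ = 7.85 with 1 df and 10.90 with 3 df: ratio 1.39. At λ = 7.85 the 3-df test has 64% power.
- 90% power needs λ = 10.51 with 1 df and 14.17 with 3 df: ratio 1.35. At λ = 10.51 the 3-df test has 78% power.

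The 3-df test therefore needs about 35–39% more subjects for the same power.

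**The case against.** The strongest reply is that this is detail for the SAP. Section 15.11 gives a general rule for exploratory endpoints and defers the rest. It says chi-square tests without naming a variant, and a chi-square test for trend would satisfy those words. The mention of ordinal data stands in the sentence on frequency tables, not in the sentence on tests.

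Part of this stands: unordered is the plain reading, not the protocol's word, and the SAP could settle it. But the protocol does name a test, places ordinal data under categorical, and gives Mann-Whitney only to continuous endpoints. That is a stated choice that fits these two ratings poorly, not a gap.

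A second reply is that the comparison above favours the rank test, because proportional odds is a consistent shift. That is fair. Against a change in spread without a shift, the 3-df test does better. With placebo 25% in each level, verum 18/32/32/18% and 200 per arm, chi-square has about 66% power and Mann-Whitney about 5%. In that example, however, neither arm is better, and the stated aim is superiority.

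A reader might also infer that a significant chi-square result would leave it unknown which arm did better. The statistic carries no sign, but the planned frequency tables would show the ratings in each arm. A two-sided Mann-Whitney p-value likewise needs a descriptive summary to show direction. Direction is not the ground for this point; power is.

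**Conclusion.** The point holds as a minor one. On the plain reading, two ordered ratings get a valid test that discards their ordering. Under the assumed distributions and proportional odds, with 200 per arm, the loss against a consistent shift is about 15 to 17 percentage points at odds ratios of 1.4 to 1.6. It shrinks to about 6 points at 2.0. The true size depends on rating distributions and effects that the protocol does not give.

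It would be wrong to infer that the trial's conclusions are at risk. Type I error is about 5% for either test. The ratings are exploratory and outside the fixed testing sequence, and the primary and major secondary analyses already use rank tests. The protocol sets no power target for the global ratings, so no stated target is missed. Global tolerability is not involved: section 15.12 only tabulates it.

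**What to change.** In section 15.11 and the Biometry entry of the synopsis, state that ordinal other secondary endpoints, namely the global efficacy ratings by subject and by investigator, are compared with the two-sided Mann-Whitney test already planned for continuous endpoints, or with a chi-square test for trend. Keep chi-square for nominal and binary endpoints, such as any use of concomitant treatment on days 1–4 and confirmed cold at Visit 2. Carry the same wording into the SAP before unblinding.

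Stratification by centre is not needed for this change, and the Mann-Whitney tests in the plan are not described as stratified. The cost is one sentence in each place, with no new data and no change to sample size.
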